If at Visit 3, again, the exercise duration is less than 4 minutes or exceeds 10 min (at the defined CWR), one additional adjustment is allowed and the CWR test will be repeated after at least one day no more than 3 days after Visit 3 (Visit 3r): Specifically, if at Visit 3 the subject is not able to maintain this work rate for more than 4 minutes, then the CWR will be decreased for Visit 3r. If at Visit 3 the exercise duration at the defined CWR exceeds 10 min, then the CWR work rate will be increased for Visit 3r. This decrease or increase corresponds to the previous or next stage of the incremental protocol (Exercise Testing Manual of Procedures in the ISF). If the exercise duration is less than 4 minutes or exceeds 10 minutes (at the defined CWR) at Visit 3r, the study participant should be excluded from further participation.

At Visit 3 the CWR test should be performed *after the pre-dose PFT, but prior to randomization and study drug administration*. At Visit 5 the CWR test should be performed *after the pre-dose PFT, but prior to study drug administration*. At Visits 4 and 6 the CWR test should commence 2 hours and 15 minutes (+/-10) min after inhalation of study drug.

IC maneuvers will be carried out at rest, at two-minute intervals during exercise, and at end of IET and CWR exercise tests.

During the exercise testing (IET and CWR), patients will be encouraged to continue the exercise by a blinded tester (defined as study staff member who is blinded to whether the subject has COPD or is an Age / Gender Matched Control). At peak exercise, patients will be asked their locus of symptom limitation (legs, breathing or both legs and breathing).

During all exercise testing, pulse oximetry must be recorded and documented; however, only the value prior to testing and the lowest value and time of occurrence will be entered into the eCRF. The test should be stopped if arterial oxygen saturation falls below 85% or an adverse event occurs during the test. In such cases, the investigator must carefully evaluate the subject following conclusion of the exercise study regarding further participation in the study. **If a SAE occurs during the test the patient will be excluded from further participation in the study.**

The exercise parameters (including start time, duration, maximal work capacity, and constant work load) from the Incremental Exercise test and from the CWR test will be recorded in the eCRF.

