### **6.3 REMOVAL OF PATIENTS FROM THERAPY OR ASSESSMENT**

Patients may be withdrawn from the trial prior to completion if any of the following criteria are observed:

1. Intercurrent illness or an adverse event, which requires discontinuation of treatment per protocol.
2. An acute COPD exacerbation (defined as an increase or new onset of more than one of the following respiratory symptoms [cough, sputum, sputum purulence, wheezing, dyspnea] with a duration of three or more days requiring treatment with antibiotics and / or systemic [oral, intramuscular or intravenous] steroids).
3. Required use of supplemental oxygen therapy.
4. Oxygen desaturation below 85% for at least 30 seconds during exercise testing.
5. Actively participating in a pulmonary rehabilitation program.
6. Request by the patient to withdraw from the study.
7. Administrative reasons (protocol violations, persistent non-compliance).
8. Decision by Boehringer Ingelheim to discontinue one or all patients.
9. During the treatment period, if the investigator judges that the patient requires initiation of chronic maintenance treatment with tiotropium.

No patient should be discontinued from the trial for a protocol violation before discussion with the clinical monitor.

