### 10.3 EXERCISE TESTS

During the initial Screening Visit (Visit 1), an incremental exercise test (IET) will be performed on a treadmill to a symptom-limited maximum (maximum work capacity). In following visits (V2, V3, V4, V5 and V6), a constant work rate exercise endurance test, (symptom-limited endurance exercise test) will be performed in a similar manner at the same constant work rate equal to 80% of the maximum work rate achieved at the IET. During all exercise tests, including the incremental test and all constant work rate tests, the extent of dynamic hyperinflation will be assessed by serial inspiratory capacity measurements (IC). Specific details of the exercise tests are described in the Exercise Testing and Quality Control Manual of Procedures filed in the ISF.

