### ***Safety issues***

**Subjects will not be allowed to perform an exercise challenge if they are known to have or are suspected of having one of the following contra-indications:**

- Recent myocardial infarction (i.e., within one year or less)
- Unstable angina
- Unstable, life-threatening or uncontrolled cardiac arrhythmias causing symptoms, haemodynamic compromise, requiring intervention or change in drug therapy during the last year
- Active endocarditis
- Acute myocarditis or pericarditis
- Symptomatic severe aortic stenosis
- Uncontrolled heart failure
- Acute non-cardiac disorder that may affect exercise performance or be aggravated by exercise (i.e., infection, renal failure, thyrotoxicosis)
- History of thrombosis and / or pulmonary embolism
- Left main coronary stenosis or its equivalent
- Moderate stenotic valvular heart disease
- Electrolyte abnormalities
- Severe untreated arterial hypertension (>160 mmHg systolic, >100 mmHg diastolic)
- Significant pulmonary hypertension
- Tachyarrhythmias or bradyarrhythmias
- Hypertrophic cardiomyopathy
- Mental impairment leading to inability to cooperate
- High-degree atrioventricular block
- Cardiac (bradyarrhythmias, ventricular tachycardia, myocardial infarction, heart failure, hypotension, and shock) and non-cardiac (musculoskeletal trauma, severe fatigue,

dizziness, fainting, body aches) complications of exercise challenges have been reported. Consequently during the test, study personnel should be alert to any abnormal event.

- Indications to stop the test must be clearly established and known by the personnel involved in testing:

Symptoms such as:

- acute chest pain,
- sudden pallor,
- loss of co-ordination,
- mental confusion,
- extreme dyspnea.

Signs such as:

- clinically significant abnormalities in ECG recordings during exercise. This includes horizontal depression of ST segment  $> 0.2$  mV, T-wave inversion, sustained ventricular tachycardia, polymorphic and / or frequent premature ventricular beats, couplets or triplets particularly of multifocal origin.
  - progressive fall in systolic pressure of 20 mmHg or more less than the previous measurement or below the resting value during exercise.
  - Exercise induced hypertension  $>250$  mmHg systolic and/or  $>115$  mm Hg diastolic.

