- If the exercise test has been stopped for one of these reasons, the subject should be monitored in the laboratory until signs/symptoms/ECG abnormalities have completely cleared. Full CPR equipment should be available in the laboratory. In case the exercise test was stopped because of any of the above detailed medical reasons **the subject will be withdrawn from the study.**

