### *Phases of incremental test:*

**Start Time (TSTART):** Marks the beginning of the Incremental Exercise Test. TSTART begins after the 3 minute warm up, when the treadmill registers the speed and grade steps.

**Time to Maximal Effort (TMAX):** The subject will be encouraged to continue exercising for as long as possible and should be encouraged to complete the time point at which they begin to fatigue. Subjects should continue to exercise (i.e., to exhaustion or maximal exercise) until:

- Limited by symptoms (i.e., is unable to continue exercising because of the discomfort associated with the exercise) or desaturation (oxygen saturation  $\leq 85\%$  for at least 30 seconds)
- Unable to continue safely (in the opinion of the supervising physician).

The Incremental Exercise Time is the duration from TSTART until TMAX (maximal effort). This excludes the warm-up and recovery periods. (Incremental Exercise Time

(Duration)= $T_{MAX} - T_{START}$  (in minutes and seconds) that will be taken from the report. Subjects who are not able to walk more than 2 minutes due to severe dyspnea or leg pain are excluded from further study. If the subject is able to walk up to or exceed 15 minutes, the test will be repeated using a 15 or 20 Watt/min incremental protocol as described above.

**Recovery:** After the maximal effort is reached, the subject should continue to walk at the lowest speed (0.6 mph=1.0 km/h) and 0% grade for at least 3 minutes to prevent pooling the blood in the legs and to accelerate lactate removal. If the subject is unable to walk it is possible to offer sitting down on a chair put on the treadmill with feet put up horizontally.

**Determining the peak work rate:** The peak work rate is equivalent to the work rate of the step in which the subject requested to stop exercising as long as it was possible to complete that step for at least 30 seconds. Otherwise the peak work rate will be equivalent to the work rate of the last completed step.

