### Data collection during the constant work rate treadmill test

The data collection will be accomplished in part by the cardiopulmonary exercise gas exchange measurement system. The system is able to provide the following variables: Speed, inclination, TMWatt (calculated from the treadmill parameters recorded electronically from the treadmill and the subject's weight), HR, VO2, VCO2, VE, VT, IC, SpO2, Ttot, Ti, Te, Vmax, VT/Ti, VT/Te (can be calculated if not provided). Because there is no way to predict the effect of the therapeutic intervention on the exercise endurance, the data collection plan has to adopt a strict timing. Only this will assure that the physiological responses will be comparable at isotime, i.e., at the time point equal to the duration of the shortest test.

In addition to adhering to the general considerations for exercise challenges described above, the following specific procedures should be adhered to during the constant work rate exercise tests:

- The subject will exercise until:
  1. limited by symptoms (i.e., is unwilling to continue exercising because of the discomfort associated with the exercise) OR

2. unable to continue safely (in the discretion of the supervising technician).

At the end of exercise, the time of exercise is recorded (minutes and seconds); the actual endurance will be taken from the cardiopulmonary test report.

- Patients will be asked to rate the intensity of dyspnea using the Borg Category Ratio Scale before the start of the exercise test, every 2 minutes during exercise and at peak exercise.

Changes in end-expiratory lung volume (EELV) will be estimated from inspiratory capacity maneuvers. These will be assessed in 2 minute intervals, in the second half (i.e., 31-59 seconds) of the minute. Techniques for performing and accepting IC measurements are described in detail in the Exercise Testing and Quality Control Manual of Procedures filed in the ISF.

- Symptom intensity ratings (Borg category ratio scale for shortness of breath and leg fatigue) will be assessed in the preceding 30 seconds (i.e., 01–29 sec) prior to the IC measurement. In the 30 sec period after the IC maneuver the blood pressure will be taken.
- ECG monitoring will be done continuously during the exercise test. Heart rate will be recorded from the ECG at 1, 2, 3, 5, 7, 10 minutes and end of exercise whatever comes first.

Recovery:

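### Appendix 10.3 makes withdrawal mandatory when a test is stopped for an undefined degree of dyspnea, although the tests are designed to end at symptom limitation and Sections 5.1.1 and 6.3 state other consequences

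*Protocol*

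**What the plan says.** Appendix 10.3 (Safety issues) gives staff a list of indications for stopping a test. Among the symptoms, next to acute chest pain and mental confusion, stands "extreme dyspnea". No Borg score, sign or decision-maker is attached to it. The consequence for every item on the list is fixed: "In case the exercise test was stopped because of any of the above detailed medical reasons", "the subject will be withdrawn from the study".

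Other parts of the protocol bear on the same event:

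- **Incremental test (Appendix 10.3).** At Visit 1 "an incremental exercise test (IET) will be performed on a treadmill to a symptom-limited maximum (maximum work capacity"), and "The subject will be encouraged to continue exercising for as long as possible".
- **Constant work rate test (Appendix 10.3, data collection).** The test ends when the subject is "limited by symptoms (i.e., is unwilling to continue exercising because of the discomfort associated with the exercise"), or when the supervising technician judges it unsafe to go on.
- **Appendix 10.5 and Sections 2.3 and 2.3.1.** Breathing discomfort is a standard answer to why the test ended. Dyspnea intensity and the locus of limitation are efficacy endpoints.
- **Section 5.1.1.** After a stop for desaturation or an adverse event: "In such cases, the investigator must carefully evaluate the subject following conclusion of the exercise study regarding further participation in the study". Only an SAE excludes automatically.
- **Section 6.3.** "Patients may be withdrawn from the trial prior to completion if any of the following criteria are observed". None of the nine criteria names dyspnea during exercise.

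**The concern.** Strong dyspnea is an expected way for these tests to end, because patients are encouraged to their symptom limit and breathing-limited patients are recruited on purpose. Exclusion 7 in Section 3.3.2 removes those limited by something other than fatigue or exertional dyspnoea. A rule that forces withdrawal for a degree of dyspnea that nobody has defined therefore overlaps with the planned end of the test.

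Two things are at stake. Before randomisation, a literal reading would narrow the population by removing some of the patients in whom breathing limits exercise. After randomisation, withdrawal would hinge on a symptom that the drug is meant to improve, so losses could differ by treatment. Sites that read the word differently could also lose patients at different rates.

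**Working it through.** **1. The passages side by side**

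| Event | Appendix 10.3, Safety issues | Elsewhere |
|---|---|---|
| Test ends in dyspnea | Mandatory withdrawal if the dyspnea is extreme (undefined) | Intended end of test (Appendix 10.3, both tests); standard answer (Appendix 10.5) |
| Listed stop reason that is also an adverse event | Mandatory withdrawal | Investigator evaluates; automatic exclusion only for an SAE (Section 5.1.1) |
| Withdrawal list | Will be withdrawn | May be withdrawn; exercise dyspnea not listed (Section 6.3) |
| Severe dyspnea in the incremental test | Mandatory withdrawal if extreme, at any duration | Exclusion if the subject cannot walk more than 2 minutes (Appendix 10.3, phases of the incremental test) |

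The overlap with Section 5.1.1 is partial. Desaturation is not on the Safety issues list, so the two rules collide only where a listed reason is also an adverse event.

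**2. Which visits reach the primary analysis**

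The full analysis set requires post-dose values at both Visit 4 and Visit 6 (Section 7.3). These are not imputed (Section 7.4), and patients are not replaced (Section 6.3).

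- Visits 1 to 3 precede randomisation. Loss there changes who is studied but causes no imbalance between treatments.
- Visit 4 is on treatment. Withdrawal there removes Visit 6, and with it the whole patient.
- Visit 5 is pre-dose after wash-out. Loss there removes the patient, but no study drug is being taken.
- At Visit 6 the primary data have already been collected.

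Treatment-related loss therefore acts through Visit 4 only.

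**3. The plan's own sample size**

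Inputs from Section 7.6: difference 100 ml, SD of change 340 ml, correlation 0.6, two-sided alpha 0.05. The SD of the within-patient difference is √(2 × 340² × (1 − 0.6)) = 304.1 ml. A one-sample t-test (noncentral t) needs N = 100 for 90% power (computed 0.903). All eight rows of Table 7.6: 1 reproduce. With 124 randomised and 20% drop-out, 124 × 0.8 = 99.2 remain, with power 0.90.

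**4. Power under assumed extra loss (illustrative)**

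The protocol gives no frequency for these stops. With a further fraction f lost, n = 124 × 0.8 × (1 − f), rounded down:

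| f (assumed) | n | Power |
|---|---|---|
| 0% | 99 | 0.90 |
| 5% | 94 | 0.88 |
| 10% | 89 | 0.87 |
| 20% | 79 | 0.82 |
| 30% | 69 | 0.77 |

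**5. Direction and size of bias (illustrative)**

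A simulation used the planning values and a true effect of 100 ml. Withdrawal at Visit 4 was driven by a latent dyspnea score whose correlation with first-period IC was 0.3, 0.5 or 1.0 in absolute value, with higher IC meaning less dyspnea. The estimate comes from patients with both periods.

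| Withdrawn on placebo (assumed) | Withdrawn on tiotropium | Estimate |
|---|---|---|
| 5% | 2.6% to 4.2% | 96.8 to 99.7 ml |
| 10% | 5.8% to 8.5% | 95.0 to 99.5 ml |
| 20% | 12.8% to 17.6% | 92.4 to 99.2 ml |
| 30% | 20.7% to 27.0% | 90.6 to 99.3 ml |

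Losses are higher on placebo, and the estimate moves modestly toward zero.

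**The case against.** The strongest reply is that context already separates the two kinds of stop. The list stands under a safety heading, is addressed to testing staff, follows a paragraph on complications, and is later described as medical reasons that need monitoring until they clear. For both tests, Appendix 10.3 distinguishes a subject limited by symptoms from one who cannot safely continue. It also gives the subject a separate signal for unexpected difficulty. Technicians are certified for this trial, and an exercise manual that is not shown may define the stop. On this reading the rule covers only staff-called emergencies and touches few patients. Section 6.3 also allows withdrawal for an adverse event that requires discontinuation under the protocol, which can accommodate part of the appendix.

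Much of this stands. A reader might infer that nothing in the protocol separates a safety stop from the planned end of a test; that goes too far. What is missing is a criterion that assigns dyspnea to one side or the other. Two points survive the reply: a mandatory consequence is attached to an undefined degree of the trial's central symptom, and the consequence differs from that in Sections 5.1.1 and 6.3.

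**Conclusion.** The conflict is in the text and should be resolved before patients exercise. Its practical size is unknown, because it depends on how sites read the term and the documents give no rate.

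Three stronger readings are not supported:

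- **That the rule removes the breathing-limited patients as a group.** This follows only if every breathing-limited stop is called extreme.
- **That it would use up the drop-out allowance.** A 10% chance at each of Visits 4 and 5 gives 1 − 0.9² = 19%, or 0.19 × 124 ≈ 24 patients, equal to the allowance of 124 − 100 = 24. But the 10% has no source. The sum also treats tests within a patient as independent, at a constant rate, in patients who have already come through the screening tests.
- **That it would seriously distort the treatment effect or favour tiotropium.** Treatment-related loss acts through Visit 4 only. In the simulation the shift is toward the null, with estimates of about 91 to 99.7 ml against a true 100 ml across assumed placebo withdrawal of 5% to 30%.

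The sample size calculation itself is sound on its stated inputs.

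**What to change.** Reconcile the Safety issues text of Appendix 10.3 with the stopping rules for the incremental and constant work rate tests in the same appendix, and with Sections 5.1.1 and 6.3. Use the same words in each place to distinguish the intended symptom-limited end of a test, including one that ends in dyspnea, from a medical safety stop. State one consistent consequence for safety stops. The sponsor's clinicians decide where the line lies and what the consequence is; no threshold or rule is proposed here.

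The cost is protocol wording and a site training note, with no extra patients or procedures. A separate eCRF field for the type of stop is optional. It would let the trial report how many tests ended in a safety stop, at the price of asking staff to classify each stop.

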#### *Subject preparation*

- Subjects should not eat, and should avoid caffeine-containing products, for at least 2 hours before any exercise challenge.
- Subjects should dress appropriately for the exercise challenge.
- On arrival in the laboratory, a detailed explanation of the testing procedure and equipment should be given to the subject, outlining the risks involved and potential complications (see *safety issues* section above).
- Before exercise, ECG electrodes are carefully placed and secured after preparing the skin to ensure good recordings (if necessary, the area of the electrode placement needs to be shaved).
- The subject is informed that it is acceptable to swallow with the mouth piece in place and that he / she must signal if he /she anticipates that within the next minute it will be necessary to stop exercising. However, should any unexpected difficulty arise at any time during the test; it should be signaled by “thumbs down”. This will be used as signal to terminate the test. The subject is advised to point to the site of discomfort if chest or leg pain is experienced.
- Good communication with the subject throughout the whole procedure increases the subjects’ confidence and helps to ensure a good effort by the subject. It is also necessary to restrict any other interaction between the attending personnel.

## INCREMENTAL EXERCISE CHALLENGE

In addition to adhering to the general considerations for exercise challenges described above, the following specific procedures should also be adhered to while preparing the test at Visit 1. The incremental ramp protocol for the COPD patients will be uniformly 10 W/min and 15 W/min for the age/ gender matched control subjects. The individualization will be programmed into the RDC system. This will assure that the laboratories will be provided with the parameters of the appropriate protocol the parameters of which will be entered in testing system.

The programmed exercise challenge test protocol provides a total of 15 steps. The target work rate (100 Watts in the COPD group and 150 Watts in the control group) is reached in the 10th step and additional 5 steps for further incrementing the work rate with the same slope. This design allows for each subject to perform the same work rate increment utilizing the same speed-range, regardless of the subject's weight, thus providing a comfortable walking speed throughout the test for everybody.

The speed will be incremented linearly from 0.6 mph to 2.2 mph in the expected range and reaches a maximum of 4 mph in the extended range. The steps of the inclination are calculated based on linearly incremented speed and work rate steps; resulting in a non-linear increase in the treadmill grade.

Entering the appropriate values in the appropriate page on the eCRF, the protocol parameters are automatically calculated and will be displayed on the screen in a table. This table should be saved as source document and will be used to select the treadmill parameters for the constant work rate test (see below).

Should the subject reach or exceed 150 Watts (step 15), the incremental test will be repeated after at least 90 minutes later using 15 Watts/min (or 20 Watts/min for control subjects) slope. The repeat Incremental Exercise Test will recalculate the slope to 15 Watts/minute with a speed range of 0.6–3.0 mph and between 0 and 150 Watts. Similarly, a protocol with 20 Watt/min ramp slope will be generated for the control subjects.

